## Abstract

**Background:**

Ghana has made progress in maternal and newborn health, but significant challenges remain, with maternal mortality at 263 per 100,000 live births and neonatal mortality at 22.8 per 1,000 live births. The Obstetric Triage Implementation Package (OTIP), which includes rapid triage protocols and midwife-led peer training, aims to improve the quality of care in a context of scarce resources. This study evaluates the effectiveness of OTIP in improving maternal and neonatal outcomes and assesses the mechanisms behind the observed effects.

**Methods:**

A cluster randomized controlled trial will assess the impact of OTIP in 25 high-volume hospitals across Ghana during the final phase of its national roll-out. Hospitals will be randomized into early and late intervention groups. A complementary regression discontinuity analysis will assess the impact of OTIP at the national level. Primary outcomes include process improvements and maternal and neonatal outcomes. Secondary outcomes will assess midwives’ knowledge and attitudes. Data sources include primary surveys of 1,250 mother-newborn pairs and 750 midwives, and administrative records from the Ghana Health Service, Ministry of Health.

**Discussion:**

A rigorous evaluation of OTIP would be crucial, not only to assess the effectiveness of a program in which the Government of Ghana is already investing, but also to assess the potential applicability of this training model to other areas, and to contribute to the academic literature by filling gaps in our understanding of how different training methods can overcome barriers to the diffusion of new practices.

**Trial registration:**

Study protocols have been approved by the Ghana Health Service (GHS) Ethics Review Committee (GHS-ERC: 022/05/24). Trial registration number: ISRCTN15629047. Registered on 04/11/2024 while participant enrollment was ongoing, 10.1186/ISRCTN15629047. The study is hence retrospectively registered.

**Supplementary Information:**

The online version contains supplementary material available at 10.1186/s12913-025-13132-7.

## Background and rationale

Ghana has made considerable progress on key human capital indicators, such as reducing infant and child mortality rates, and has seen a significant rise in institutional deliveries over the past decade [1]. However, many hospitals still face shortages of critical resources needed to treat high-risk patients, while the growing workload negatively impacts the quality of care provided [2].

Ghana’s maternal mortality was 263 per 100,000 live births in 2020 [3] and neonatal mortality rate 22.8 per 1,000 live births, both remaining behind targets set by the United Nations Sustainable Development Goals [4].

The need to build the capacity of healthcare providers is widely acknowledged. Given the common challenges of low adherence to best practices and the limited fiscal space in government budgets, officials are emphasizing the need to better utilize existing resources. Peer-to-peer learning, supervision, and support—through feedback and mentoring—are seen as essential for maintaining quality.

The Obstetric Triage Implementation Package (OTIP) is designed to address these needs. OTIP consists of a 1-week on-site training on clinical knowledge to quickly assess and prioritize the care of pregnant women, with the goal of promptly and accurately identifying the severity of a patient’s condition, determine the appropriate level of care, and ensure that those with the most critical needs receive immediate attention.

A key innovation of OTIP is the designation of up to ten midwives per hospital as ‘Champions’—those selected to attend onsite training and lead the implementation of the new triage protocol. These Champions are responsible for training their peers, as well as monitoring and motivating the adoption of the protocol among colleagues and setting up and maintaining a triage room.

Pilot studies have demonstrated significant reductions in patient waiting times, highlighting the potential to improve both the efficiency and quality of service delivery [5, 6], consistent with evidence from on-the-job training by more experienced or skilled workers in the education sector [7, 8]. However, the scalability of OTIP and its effectiveness remain uncertain. Conducting rigorous research on its implementation at scale is critical, as promising interventions often face challenges in scaling up [9].

A rigorous evaluation of OTIP Champions would be crucial not only for assessing the potential application of this training model to other areas of GHS, such as essential care for small babies and kangaroo mother care, but also for contributing to the academic literature by addressing gaps in our understanding of how different training methods can overcome barriers to the diffusion of new practices [10].

### Objectives

The project’s key research questions are as follows:What is the impact of OTIP on the quality of service during labor and delivery, as well as on maternal and neonatal survival, and on neonatal health outcomes? To what extent does OTIP affect clinical knowledge and midwives’ attitudes? 

### Methods and trial design

This study uses a cluster randomized controlled trial (cRCT) to evaluate the impacts of the introduction of the OTIP Champions program across high-volume hospitals in the final phase of its nation-wide rollout. The cRCT will be integrated into the final phase of the national rollout of the OTIP training program, covering the Central, Greater Accra and Western regions. 12 of the 25 hospitals are randomly assigned to receive OTIP training in September 2024, and the remaining 13 receive OTIP approximately 4 months later. Figure 1 is the design flow diagram. SPIRIT reporting guideline were used [11].

**Fig. 1 Fig1:**
[figure not shown]
Randomization flow Diagram

#### Study setting

The Government of Ghana, through Ghana Health Services, is rolling out OTIP to all high-volume hospitals (defined as hospitals with more than 1,200 births in 2022) in different regions of the country. In 2023, the average total number of deliveries in these high-density hospitals was 2,146. The average maternal mortality rate was 110 per 100,000 live births, and the average neonatal mortality rate was 8.21 per 1,000 live births. In hospitals across Ghana, the average total number of deliveries in 2023 was lower, at 1,688. The average maternal mortality rate was slightly higher at 126 per 100,000 live births, while the average neonatal mortality rate was slightly lower at 7.7 per 1,000 live births.

#### Eligibility criteria

The cRCT will focus on the 25 hospitals that will receive the OTIP program during the final phase of the national roll-out, which has been planned in three phases (see Supplementary Materials S.3 for names of study sites). The first two phases of the roll-out were completed by April 2024. The third and final phase of the rollout was started in September 2024, covering all eligible hospitals, 25 in total, in Greater Accra, Central and Western regions.

Within each study hospital, target participants will be mothers that delivered in the hospital within the last two months prior to data collection. They will not be selected if they are facing post-birth complications, or if they are below the age of 18 and a guardian is not present. Data from mothers recruited in January 2024 will be the basis for the impact evaluation. We in addition collect information from mothers who were present prior to intervention implementation. These will however not be exposed to the OTIP intervention.

We will further conduct interviews with individuals who will perform the intervention, e.g. midwives. We will interview those that are selected to be OTIP champions, and a random sample of non-champion midwives on permanent contracts in the maternity department, including those in charge of wards and clinics. We will also administer online surveys to all the midwives on permanent contracts working in each hospital to collect data on clinical knowledge (1,338 midwives in total).

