#### Outcomes

We consider two sets of primary outcomes:Process variables: Representing the actual medical care received by mothers and their new-borns (e.g., time until initial assessment; assessment received upon arrival; doctor intervened if complications during labour and delivery at the hospital; postnatal checks).Maternal and neonatal outcome variables: Including the health of pregnant women and new-borns (e.g. maternal and neonatal mortality; complications during labour and delivery at the hospital; APGAR scores).

To examine mechanisms behind potential impacts of OTIP on the primary outcomes, we further consider secondary outcomes:Hospital staff outcomes: Such as improved knowledge and midwives’ attitudes capturing their perceptions of autonomy, empowerment and motivation.

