#### Sample size, sampling, and recruitment

The total targeted sample size for the cRCT will be in-person interviews with 750 staff, and 1,250 patients (mothers) per data collection round. In addition to the in-person survey we will administer online surveys to all the midwives on permanent contracts working in each hospital to collect data on clinical knowledge (1,338 midwives in total).

The patients target sample sizes proportional to each hospital’s delivery caseload in August-October 2023. This results in a minimum sample size of 35 and a maximum sample size of 65 per hospital. The inclusion criteria will be those who delivered in the hospital within the last two months, primarily from labor wards, postnatal wards, and postnatal care clinics. This eligibility criteria implies that in each survey round, we will interview a new cross section of 1,250 mothers. For mothers 18 years or younger, interviews will only be conducted if a guardian is present and provides consent in addition to the mother doing so herself. Mothers will only be approached for interview if not in distress due to, for example, having lost their child during labor. We will cross-check with hospital staff whether mothers can be approached or not.

The sample of midwives for these interviews will consist of the 10 midwives nominated by management or their peers to become champions (of whom 7 will ultimately be selected for training) and a random sample of 20 other midwives with permanent contracts in the maternity department, resulting in a total midwife sample of 750 midwives. We will not interview any students or staff on temporary contracts in the hospital. We aim to interview the same set of midwives throughout the study.

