#### Assignment of interventions

Randomization was conducted using Stata version 16 by researchers at the IFS. The randomization determined whether a hospital would receive the intervention earlier or later. The decision whether a patient is assigned to the intervention or control group therefore depends on the timing of inclusion. By end February 2025 all hospitals will have received the intervention and hence by then every patient will be included in treatment. There is no blinding. Inclusion in the study for assessment of intervention effectiveness will be completed by the end of January 2025.

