#### Data collection and management

We will rely on two main sources of data. For the cRCT, we will mainly rely on primary collected data from patients (mothers), and from midwives through in-person interviews. To promote data quality, all enumerators attend a week-long training session before data collection. This includes classroom-based training as well as training in hospital settings. It also covers how informed consent should be obtained, implying that informed consent will be acquired by well-trained and vetted data collection staff before the commencement of any data collection. Lead enumerators were also involved in two weeks of extensive piloting of the survey instruments.

For the regression discontinuity design, we will utilize the District Health Information Management System II (DIMS II), an electronic platform managed by GHS to collect, record, and analyze health service data nationwide. We will use key indicators such as deliveries and mortality for mother and new-born pairs at the hospital and monthly level from before, during and after OTIP implementation.

Administrative records and collected data will be recorded electronically using password-protected laptops. Once data collection is completed, all data will be promptly uploaded to an encrypted folder and/or deleted from the laptops. Access to the encrypted folder will be restricted to the research team, with participants’ identities anonymized in any reports derived from the research.

Once results are published, an anonymized version of the dataset will be released publicly without any personally identifying information.

The project is compliant with the Ghana Data Protection Act 2012 Act 846, and the UK Data Protection Act 1998.

For further details on data management: please refer to the project’s management registration: https://ifs.org.uk/sites/default/files/2024-11/Data-protection-V2.pdf. Data availability is outlined in online supplemental material S2.

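### Mortality and labour complications are primary and estimated by randomised arm, but the only patient source described for the cRCT is an interview sample whose entry depends on those outcomes

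*Protocol article*

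**What the plan says.** All references are to the protocol article.

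- **Outcomes** lists the primary maternal and neonatal variables as including "maternal and neonatal mortality; complications during labour and delivery at the hospital; APGAR scores". It does not say which design or data source each one belongs to.
- **Statistical methods** applies equation 2, indexed by mother or baby, to both process outcomes and maternal and neonatal outcomes, with allocation as the treatment term.
- **Sample size and power** (Table 1) powers the mother/child outcomes on 1,250, which is the interview sample.
- **Data collection and management** states: "For the cRCT, we will mainly rely on primary collected data from patients (mothers), and from midwives through in-person interviews".
- **Eligibility criteria** says of mothers: "They will not be selected if they are facing post-birth complications".
- **Sample size, sampling, and recruitment** adds: "Mothers will only be approached for interview if not in distress due to, for example, having lost their child during labor", and "We will cross-check with hospital staff whether mothers can be approached or not". Each round is a new cross-section of mothers.
- **Assignment of interventions** states: "There is no blinding".
- **Data collection and management** also says, for the regression discontinuity design (RDD): "We will use key indicators such as deliveries and mortality for mother and new-born pairs at the hospital and monthly level". **Methods for additional analyses** presents the RDD as the route to mortality effects.

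**The concern.** Randomisation balances the women who deliver in the two sets of hospitals. It does not balance the women who are later interviewed if interview depends on something the intervention is meant to change. Here, interview depends on the mother being alive, on her not currently having a post-birth complication, and on her not being in distress, which the death of a baby can cause. All three arise after allocation, and each is either a primary outcome or closely tied to one.

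Two consequences follow. If the programme prevents poor outcomes and the same share of affected mothers is screened out in both arms, the observed difference shrinks. If unblinded staff advise differently in early and late hospitals, a difference can appear where there is none.

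The attrition test and inverse probability weighting in Statistical methods do not reach this problem. A mother who was never approached is not lost from a panel, because mothers are sampled afresh in each round.

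**Working it through.** **1. Inputs from the protocol.** Study setting gives, for high-volume hospitals in 2023, a mean of 2,146 deliveries, maternal mortality of 110 per 100,000 and neonatal mortality of 8.21 per 1,000 live births. I apply these rates to deliveries as an approximation. Sample size and power gives 25 hospitals, 50 mother-newborn pairs each, two-sided alpha 0.05, power 0.8, and ICC 0.01 for maternal and neonatal outcomes.

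**2. The plan's own figure.** With equal arms and normal quantiles (1.960 + 0.842 = 2.802):

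MDE = 2.802 × √[(4/N) × (1 + (m − 1) × ICC)]

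- ICC 0.01: 2.802 × √(0.0032 × 1.49) = 0.193 (Table 1: 0.196).
- ICC 0.1: 2.802 × √(0.0032 × 5.9) = 0.385 (Table 1: 0.390).

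Table 1 reproduces within 1.5%. For a rare event the SD is √[p(1 − p)]. For neonatal death this is 0.0902, so 0.196 SD is 17.7 per 1,000, against a rate of 8.21. For maternal death it is 0.0331, so 0.196 SD is 6.5 per 1,000, against a rate of 1.1. Even with no selection, the survey's detectable effect exceeds the whole event rate.

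**3. Deaths the survey could hold.**

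- Maternal: 1,250 × 0.0011 = 1.4 in an unselected sample, and 0 from mothers' own interviews.
- Neonatal: 1,250 × 0.00821 = 10.3 in an unselected sample. If a share q of affected mothers is not interviewed, the observed risk is p(1 − q) / [p(1 − q) + 1 − p]. Assumed shares of 50%, 80% and 95% give about 5.2, 2.1 and 0.5 deaths.

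**4. Effect on a comparison of complications (risks and shares assumed).**

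| True risks (late vs early) | Share screened out | Observed risks | Observed difference |
|---|---|---|---|
| 15% vs 10% | 25% in both | 11.7% vs 7.7% | 4.0 points |
| 15% vs 10% | 50% in both | 8.1% vs 5.3% | 2.8 points |
| 15% vs 10% | 80% in both | 3.4% vs 2.2% | 1.2 points |
| 15% vs 15% | 50% vs 30% | 8.1% vs 11.0% | 2.9 points, spurious |

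The true difference in the first three rows is 5.0 points. The documents give no screening share, so these rows show direction and range, not an estimate.

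**5. Whether the RDD fills the gap.** It compares hospitals on either side of 1,200 deliveries in 2022. All 25 trial hospitals are in the programme because they exceed that threshold, so both randomised arms lie on the same side. The RDD cannot give the effect by allocation, and the outcome its specification defines is mortality, not complications or APGAR.

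**6. What routine data would give.** Participant timeline puts early training in October 2024 and late training in February 2025, leaving November to January. I assume the 25 hospitals have the average volume of all high-volume hospitals.

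- Deliveries: 25 × 2,146 × 3/12 = 13,412, or about 536 per hospital.
- Expected deaths: 13,412 × 0.00821 = 110 neonatal and 13,412 × 0.0011 = 15 maternal.
- Neonatal MDE at ICC 0: 2.802 × 0.0902 × √(4/13,412) = 4.4 per 1,000, which is 53% of the rate.
- At ICC 0.01 the design effect is 1 + 535.5 × 0.01 = 6.4, and the MDE is 4.4 × √6.4 = about 11 per 1,000.

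No covariate adjustment is included.

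**The case against.** The strongest reply is that the protocol never says mortality will be measured by survey. It sends mortality to the RDD on routine data, the Abstract names administrative records as a source, and the cRCT relies only mainly on interviews. This stands. A reader might infer that the trial plans to count deaths by interviewing mothers, and the text does not go that far. What remains is that mortality is primary, equation 2 covers maternal and neonatal outcomes by arm, and no source other than the interviews is described for that comparison.

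Other limits also stand.

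- A reader might infer that every woman with a complication is excluded. The rule concerns current post-birth complications, whereas the outcome is complications during labour and delivery. Mothers can be interviewed up to two months after birth, so those whose complications have resolved stay eligible.
- Bereaved mothers are excluded if in distress. The text does not exclude all of them.
- Nothing removes low-APGAR babies by rule.
- Consulting staff before approaching a mother is an ethical safeguard. The documents give no evidence that it works differently by arm, only that it could.
- Recruitment is "primarily from labor wards, postnatal wards, and postnatal care clinics". One might infer that the postnatal-check outcome is selected too, but that outcome is undefined and may cover checks before discharge.
- The attrition weighting has a proper use for the midwives, whom the team aims to re-interview. It is not offered as a remedy for mothers' eligibility.
- Sampling frames and approach logs may be in a full protocol that is not shown, so their absence from the article is not the fault raised here.

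**Conclusion.** The concern holds in this form: primary outcomes are to be compared by randomised arm, and the one patient sample described for that comparison is entered conditionally on those outcomes or their close correlates. The strength differs by outcome. Maternal death is unobservable from the mother's interview. Neonatal death is under-observed to an unknown degree. Complications are selected through a correlate.

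The bias can run in either direction and cannot be sized from the documents; every screening share above is an assumption. The counts of 1.4 and 10.3 deaths rest only on the protocol's rates and sample size. Neither the attrition weighting nor the RDD supplies an unselected comparison of the arms.

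An all-deliveries comparison would avoid the interview selection but would be imprecise, with a neonatal MDE of about 4.4 to 11 per 1,000 across ICC 0 to 0.01. About 15 maternal deaths would say little about maternal mortality. These figures assume average volume in the 25 hospitals.

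**What to change.** 1. State the data source and population for each primary outcome, and the design it belongs to.
2. Remove maternal and neonatal mortality from the survey-based primary family.
3. For the cRCT, analyse mortality from the planned hospital-month administrative data, for all deliveries in the 25 hospitals, by allocation, in the months between early and late training, with each hospital's pre-period rate as covariate. Define the window from actual training dates, since Methods and trial design gives September 2024 for the early group and Participant timeline gives October.
4. Do the same for complications and APGAR only if those data record them; the protocol names only deliveries and mortality as examples.
5. Label survey outcomes as applying to surviving, approachable mothers, and report the numbers not approached by arm and reason.
6. Leave the safeguard for distressed mothers as it is.

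The cost is a wording change, one added analysis of data the team already plans to obtain, and a simple count of mothers not approached. The downsides are coarser clinical detail and low precision. The mortality comparison should be presented as unbiased with respect to interview selection but imprecise, and a null result should not be read as evidence of no effect.

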#### Intervention

The OTIP Champions Program, developed by the non-governmental organization Kybele, Inc. in partnership with GHS, consists of a 1-week on-site training on clinical knowledge and a new triage protocol to quickly assess (in less than 10 min since arrival) and prioritize the care of pregnant women (using color-coded wristbands), with the goal of promptly and accurately identifying the severity of a patient’s condition, determine the appropriate level of care, and ensure that those with the most critical needs receive immediate attention. At the core of its design, OTIP integrates rapid and accurate patient assessment and care planning as a routine part of midwives’ practice [12].

The intervention also introduces a dedicated obstetric triage area in hospitals, where midwives systematically evaluate the patient’s obstetric and medical history, vital signs and labor progress on a standardized triage assessment sheet, resulting in a categorization of high, intermediate, or low risk, and the application of a corresponding color-coded patient wristband. See Fig. 2 for more details on categorization. A care plan is developed and documented based on the diagnosis and risk status. High-risk pregnancies require immediate intervention, with a doctor involved, intermediate-risk cases require careful and frequent monitoring, and low-risk cases proceed to normal delivery with the assistance of a midwife.

